## Abstract

**Background:**

Impaired balance and mobility are common among rehabilitation inpatients. Poor balance and mobility lead to an increased risk of falling. Specific balance exercise has been shown to improve balance and reduce falls within the community setting. However few studies have measured the effects of balance exercises on balance within the inpatient setting.

The aim of this randomised controlled trial is to investigate whether the addition of circuit classes targeting balance to usual therapy lead to greater improvements in balance among rehabilitation inpatients than usual therapy alone.

**Methods/Design:**

A single centre, randomised controlled trial with concealed allocation, assessor blinding and intention-to-treat analysis. One hundred and sixty two patients admitted to the general rehabilitation ward at Bankstown-Lidcombe Hospital will be recruited. Eligible participants will have no medical contraindications to exercise and will be able to: fully weight bear; stand unaided independently for at least 30 seconds; and participate in group therapy sessions with minimal supervision.

Participants will be randomly allocated to an intervention group or usual-care control group. Both groups will receive standard rehabilitation intervention that includes physiotherapy mobility training and exercise for at least two hours on each week day. The intervention group will also receive six 1-hour circuit classes of supervised balance exercises designed to maximise the ability to make postural adjustments in standing, stepping and walking.

The primary outcome is balance. Balance will be assessed by measuring the total time the participant can stand unsupported in five different positions; feet apart, feet together, semi-tandem, tandem and single-leg-stance. Secondary outcomes include mobility, self reported physical functioning, falls and hospital readmissions. Performance on the outcome measures will be assessed before randomisation and at two-weeks and three-months after randomisation by physiotherapists unaware of intervention group allocation.

**Discussion:**

This study will determine the impact of additional balance circuit classes on balance among rehabilitation inpatients. The results will provide essential information to guide evidence-based physiotherapy at the study site as well as across other rehabilitation inpatient settings.

**Trial registration:**

The protocol for this study is registered with the Australian New Zealand, Clinical Trials Registry: ACTRN=12611000412932

## Background

Patients admitted to a general rehabilitation ward often present with poor mobility, impaired balance and reduced ability to carry out activities of daily living [1,2]. These impairments usually result from a primary diagnosis of fall, orthopaedic complaint (commonly hip fracture), neurologic condition or frailty.

Balance is defined as the ability to maintain the projection of the body's centre of mass within manageable limits of the base of support [3]. Poor balance and mobility impairment have consistently been associated with an increased risk of falling among rehabilitation inpatients and among patients discharged home from a rehabilitation setting [4-8].

Falls are a frequent occurrence among patients admitted to a rehabilitation ward [9,10] and once discharged home the likelihood of falling is significantly greater for these people than that for the general community [11,12]. Falls are the leading cause of injury related hospitalisations in NSW, accounting for 39% of all such hospitalisations in NSW in the period 2005/06 to 2007/08. Almost two thirds of hospital admissions for people aged 65 and over are falls related. In 2006/07 this equated to 49,485 hospitalisations. Total health care costs in NSW associated with fall injuries in 2006/07 was estimated at $558.5 million [13], more than any other single cause of injury. In addition to the financial cost, falls also place significant burden on an individual’s quality of life.

Specific balance exercise has been shown to improve balance and reduce falls in the general older population. There have been two systematic reviews looking at exercise interventions aimed at improving balance [14] or decreasing falls [15] in older people. Howe et al. [14] found that programmes that involved balance and coordination were effective interventions for improving balance. Sherrington et al. [15] found that exercise programmes reduced falls and programmes that specifically included challenging balance activities such as exercising without using the hands for support and narrowing the base of support were associated with a greater fall prevention effect. This is consistent with a “task-specific” approach to exercise prescription i.e., that greater improvements are seen when exercises are most similar to the task for which improvement is sought [16].

Few studies have measured the effects of balance exercises on balance within the inpatient setting. While Sherrington et al. [17] found that balance significantly improved after 2 weeks of either weight-bearing balance exercise or a non-weight bearing strengthening program for inpatients with hip fracture, no difference was found between the two exercise groups. Haines et al. [10] reported a reduction in incidence of falls in the rehabilitation inpatient setting after a targeted falls prevention programme incorporating individualised balance exercises. However, another targeted multifactorial intervention incorporating balance exercise showed no effect on incidence rate of falls compared with usual care [18]. Balance was not assessed/measured by either Haines et al. [10] or Cumming et al. [18].

The exercise principles found to be associated with a greater impact on falls in the Sherrington et al. review [15] (i.e., exercising without using the hands for support and narrowing the base of support to challenge postural adjustments in standing) will be implemented in this trial to determine whether similar improvements in balance can be made among patients undertaking general rehabilitation. To our knowledge this will be the first study to examine the effects of a balance exercise programme on balance among patients admitted to a general rehabilitation ward. The primary research question is:

Does the addition of balance circuit classes to usual therapy lead to greater improvements in balance among rehabilitation inpatients than usual therapy?

## Methods/Design

### Design

A single centre, randomised controlled trial with concealed allocation, assessor blinding and intention to treat analysis with three month follow up will be conducted among 162 rehabilitation inpatients. Figure 1 gives an overview of the study design.

**Figure 1 F1:**
[figure not shown]
Flow of participants.

### Participants

All patients admitted to the adult general rehabilitation ward at Bankstown-Lidcombe Hospital will be screened for study eligibility. Patients will be eligible if they are: admitted to the ward for rehabilitation; are able to stand for 30 seconds without physical assistance or the help of an assistive device; have no contraindications to exercise, such as uncontrolled hypertension or unstable cardiac disease; are able to fully weight bear as ordered by a medical officer; and are suitable for a group exercise class with minimal supervision as determined by the treating physiotherapist. Patients with a known multi-resistant organism infection or other infection that would pose a significant risk to others in a group setting (e.g. Methicillin-Resistant Staphylococcus Aureus, Vancomycin Resistant Enterococci, Tuberculosis) will be excluded.

Patients with a Mini Mental State Examination (MMSE) score of more than 17 will be asked to give informed consent to study participation. Consent will be sought from a ‘person responsible’ for patients who score 17 or less on the MMSE as well as for individuals who score more than 17 but treating staff consider to have a cognitive impairment that would hamper the ability to give informed consent. Interpreters will be used for consent and study assessments as required.

The South West Sydney Local Health District Human Research Ethics Committee (HREC) approved the study protocol (HREC/10/LPOOL/187).

### Randomisation

A concealed allocation procedure (numbered sealed opaque envelopes) will be used to randomly assign participants to intervention or usual-care control groups after consent and baseline measurements are performed. The allocation schedule will be computer generated using randomly ordered blocks of four and six. The schedule and sealed opaque envelopes will be prepared by an allied health staff member at the study site not involved in study recruitment or intervention.

### Intervention

All participants will receive usual therapy consisting of assessment and treatment by the multidisciplinary ward team at Bankstown-Lidcombe Hospital. Patients are predominately treated within a group setting in physiotherapy with additional one to one sessions as required with the focus being on weight bearing exercises. Patients are seen once or twice per day and on most would spend at least two hours per day in physiotherapy. The majority of physiotherapy practice occurs within the rehabilitation gym. Physiotherapy staff members are not rostered to work on weekends or public holidays. Staffing consists of two full time physiotherapists and a half-time physiotherapy assistant for twenty beds.

The intervention group will also receive six 1-hour standing balance circuit classes over a two-week period. Sessions will be run each Monday, Wednesday and Friday unless physiotherapy staff members are absent due to a public holiday. Following the two-week period, participants in the intervention group will be invited to continue with the balance circuit classes until discharged from hospital. Participants in both groups will receive usual multidisciplinary team care (e.g. outpatient therapy) after discharge. This may include outpatient physiotherapy performed either within the hospital in an outpatient setting or in the patient’s home. Physiotherapy intervention as an outpatient would generally be twice a week for six weeks.

The standing balance circuit class will comprise seven stations, each station consisting of a different exercise. The class will be supervised by one to two physiotherapy staff members (this may include a Physiotherapy Assistant) with a maximum of eight participants. The staff members running the class will be encouraged to increase the difficulty of the exercise depending on the ability of individual patients. Class participants will spend six minutes at each exercise station and will use six of the seven stations during each session. All stations have been designed to challenge postural adjustments while standing and stepping. This challenge will be achieved by performing exercises without the use of hands for support and by narrowing the base of support as able. Participants will be progressed to more challenging balance exercises as deemed appropriate by the treating physiotherapist. The amount, or dosage of exercises completed at each station will be recorded. The seven balance stations are outlined in Table 1.

**Table 1 T1:** Balance stations

**Station**	**Exercise**	**Progression**	**Counting/recording**
**Catching and passing**	Patient to catch and pass a ball with the therapist or another patient	To increase the difficulty of this task the ball can be passed to a distance further than arm’s reach. The task difficulty may also be increased by the patient decreasing their centre of balance by standing with their feet closer together or stand on an unstable surface such as thick foam rubber.	Each attempted catch to be recorded as one repetition.
**Stepping forward**	Patient to step forward with one leg then step back, continuing with the alternate leg.	To increase the difficulty of the task a block can be used to step up onto.	Every step forward and back to be recorded as one repetition
**Sideways stepping**	Patient to step sideways.	To increase difficulty of the task the patient can increase their step length or step over an object.	Each step sideways to be recorded as one repetition.
**Stepping grid**	Patient to step to targets on a board. There should be four targets (one to the right side, one to the left side, one in front of the right foot and one in front of the left foot	To increase difficulty of the task the targets can be moved to a distance further away from the patient. Additional targets may also be placed behind the person to increase the difficulty	Each step is recorded as one repetition
**Weight shift forwards and backwards**	Patient to shift weight forwards and backwards using a sway meter [19]. Technology such as the Wii platform may be used instead of the Sway meter	To increase the difficulty of the task the patient can follow a shape in various directions	Each full movement is recorded as one repetition
**Heel raises**	Patient to stand on toes, then lower self down till the feet are flat	To increase the difficulty of the task the patient can perform the heel raises on the edge of a block or on one leg.	Each heel raise is recorded as one repetition
**Reaching and moving objects**	Patient to reach for an object on one side of their body than move the object to the other side using the same arm	To increase the difficulty of the task the patient may decrease their centre of balance by standing with their feet closer together or stand on an unstable surface	Each movement of the object is recorded as one repetition.

### Outcome measures

Demographic data will be collected by baseline interview and from the medical record and will include age, sex, presenting diagnosis, usual pre-morbid type of residence, discharge location, pre-morbid level of function (whether the participant could climb a flight of stairs and walk 800 m in the three months prior to hospital admission), 12 month fall history, rehabilitation length of stay and total hospital length of stay.

#### Primary outcome

The primary outcome measures will be balance at two weeks and at three months after randomisation. This will be assessed using a composite balance measure with five balance tests: feet apart, feet together, semi-tandem (heel of one foot beside the big toe of the other foot), tandem and single leg stance. Each test will be performed without aid or upper limb support and timed up to a maximum of 10 seconds (range = 0 to 50 sec) with stand by assistance from the therapist.

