### Sample size calculation

A sample of 162 participants will be required to detect a between-group difference of 3 secs for the five balance tests (assuming a standard deviation of 9, power = 80%, p = 0.05, correlation between baseline and follow-up measures 0.65 and 15% drop out rate). Data from a previous study [4] indicate that 3 secs is likely to be approximately 15% of discharge values and we consider an effect of this size to be a clinically worthwhile.

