### Statistical analysis

Between group differences in the primary outcome and secondary measures at the two week and three month follow-ups will be analysed using ANCOVA models where baseline values are entered as covariates. Dichotomous outcomes will be analysed via logistic regression models. Primary analyses will use an intention-to-treat approach. A secondary per protocol analysis will be undertaken using data from those who participated in at least three of the six intervention sessions.

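### Balance is primary at both two weeks and three months, but the trial is sized for one unspecified comparison at 0.05 and no rule says how the two results decide the primary question

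*Protocol article*

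**What the plan says.** The Primary outcome section of the protocol article names two primary measures: "The primary outcome measures will be balance at two weeks and at three months after randomisation". The Statistical analysis section then says: "Between group differences in the primary outcome and secondary measures at the two week and three month follow-ups will be analysed using ANCOVA models", with the baseline value as covariate. It describes no joint test of the two follow-ups and no order of testing, and it gives no significance threshold.

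The Sample size calculation section has one target, "to detect a between-group difference of 3 secs for the five balance tests", and one set of inputs: "assuming a standard deviation of 9, power = 80%, p = 0.05", "correlation between baseline and follow-up measures 0.65" and "15% drop out rate". It does not say whether the target applies at two weeks, at three months or at both.

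The Background ends with a single yes/no research question on whether balance improves more with the added classes. The Abstract likewise treats balance as one primary outcome. Neither says which time point gives the answer.

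**The concern.** One question is to be answered by two results of equal standing, and the protocol does not say how they combine. If they agree, nothing is lost. If they differ, the trial could be called positive because one time point was significant, or negative because the other was not, and that choice could be made after the data are seen.

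A split result is plausible. The scheduled classes form a two-week block, continuation is by invitation and stops at discharge, and both groups may have outpatient therapy afterwards. An early difference could fade by three months.

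The two obvious readings each break one of the stated design figures. Counting either result raises the type I error above 5%. Requiring both lowers the power below 80%.

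**Working it through.** **Inputs from the Sample size calculation section.** Difference 3 s, SD 9 s, alpha 0.05, power 80%, baseline-to-follow-up correlation 0.65, dropout 15%, total 162.

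**Assumptions, not in the document.** Two-sided tests, each at 0.05 (the 0.05 appears only as a sample size input). Equal allocation. The 0.65 applies at both follow-ups. The correlation between the two follow-up scores, r12, is not given, so a range is shown.

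**1. The plan's own figure.** The ANCOVA residual SD is 9 × √(1 − 0.65²) = 9 × √0.5775 = 6.84 s. The number per arm is 2 × (1.960 + 0.842)² × 6.84² / 3² = 81.6, so 82 per arm or 164 in total before dropout. Dividing by 0.85 gives 193. The stated 162 therefore matches the calculation without the dropout allowance and does not reproduce with it. That is a separate problem, but it affects step 4.

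**2. Correlation of the two test statistics.** After adjustment for baseline, ρ = (r12 − 0.65²) / (1 − 0.65²) = (r12 − 0.4225) / 0.5775. For example, r12 = 0.65 gives 0.2275 / 0.5775 = 0.39, and r12 = 0.80 gives 0.3775 / 0.5775 = 0.65.

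**3. Type I error if either time point counts.** This is 1 − P(|Z1| < 1.96 and |Z2| < 1.96) for a bivariate normal with correlation ρ. With independent statistics it is 1 − 0.95² = 9.75%, which is the upper limit.

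| r12 (assumed) | ρ | Chance of at least one false positive |
|---|---|---|
| 0.42 | 0 | 9.75% |
| 0.65 | 0.39 | 9.3% |
| 0.80 | 0.65 | 8.5% |
| 0.90 | 0.83 | 7.6% |
| 0.95 | 0.91 | 6.9% |

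**4. Power if both must succeed, for a true 3 s effect at both times.** The standard error is 6.84 × √(4/N), and the expected Z is 3 divided by it.
- N = 162: SE 1.075, expected Z 2.79.
- N = 138 (162 × 0.85 = 137.7): SE 1.164, expected Z 2.58.

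The probability that both statistics exceed 1.96 follows from the same bivariate normal.

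| N analysed | One test | Both, r12 = 0.65 | Both, r12 = 0.80 |
|---|---|---|---|
| 162 | 80% | 67% | 70% |
| 138 | 73% | 58% | 62% |

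**5. Separating the two causes.** At 138, single-test power is already 73%, so about 7 points of the gap from 80% come from the missing dropout allowance. Requiring both costs a further 11 to 15 points there (73 − 62 and 73 − 58). With all 162 analysed it costs about 10 to 13 points (80 − 70 and 80 − 67).

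**The case against.** The strongest objection is that this is a condensed article. Multiplicity rules usually sit in the statistical analysis plan, and their absence here is no finding. That is right as far as a missing adjustment goes, and no such complaint is made. What remains is what the protocol itself fixes: two primary time points of equal rank, beside a sample size for one comparison that it does not identify. Which endpoint is primary and which comparison is powered are protocol-level choices. A later plan that ranked the two would be changing the Primary outcome section, not filling it in.

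A reader might infer that the trial simply runs a 9% false-positive risk. The document does not support that. The figure needs an either-counts rule, which is nowhere written, and if both are required the primary type I error is at most 5%. It also needs 0.05 per test and a correlation that the protocol does not supply; at high correlations the excess shrinks to about 2 points.

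A reader might also blame the two endpoints for the whole drop to 58–62% power. Part of that is the dropout shortfall.

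Nor does the document make two weeks the deciding time point. Classes may continue until discharge, and the 3 s target is justified by reference to discharge values.

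Finally, both time points use one instrument and one model and were named in advance, so there is little room to switch outcomes. That stands, but the emphasis between the two could still be chosen afterwards.

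**Conclusion.** The point holds in conditional form. The protocol declares two co-primary time points and powers one unnamed comparison at an undivided 0.05, without saying how the two results answer its single question.

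Under an either-counts rule, the false-positive risk is above the nominal 5% at every correlation examined. Under a both-required rule the error is controlled, but the stated 80% power is not met even with no dropout at all. The size in each case rests on two-sided tests at 0.05 each and on an assumed correlation between the follow-ups. The document does not settle which of the two consequences applies, and that open choice is the defect. It bears on the trial's main conclusion.

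**What to change.** Before unblinding, name one time point as the single primary outcome. Test the other as the key secondary, claimed as confirmatory only if the first is significant at two-sided 0.05. State in the Sample size calculation section which comparison the 162 refers to. Two weeks is the natural first choice because it is the end of the six-class block, but the investigators must confirm it, since the protocol does not tie the calculation to that visit.

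This takes two or three sentences, keeps the full 0.05 for the first-ranked time point and costs it no power. The price is that an isolated effect at the second-ranked time point could not be claimed as confirmatory.

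The alternatives also close the gap but cost more. Requiring both lowers power as shown above. Testing each at 0.025 holds the overall error to at most 4.9%, but cuts power per test from 80% to 71% with 162 analysed, or from 73% to 63% with 138. Holding 80% power at 0.025 would need 99 per arm, which is 198 completers, or 198 / 0.85 = 233 recruited.

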#### Secondary outcomes

Secondary outcomes will include mobility, self reported physical functioning, fall incidence and hospital readmissions.

Mobility will be assessed using the lower extremity Summary Performance Score [20] version of the Short Physical Performance Battery [21]. This battery gives a composite score based on timed performance of three mobility tasks: the ability to stand up for 10 seconds with feet in different positions (together side by side, semi-tandem and tandem), 4-metre walk and time to rise (stand-up) from a chair five times.

Self reported physical functioning will be assessed using the Basic Mobility and Daily Activity domains of the Computer Adaptive Testing version of the Boston University Activity Measure for Post Acute Care (AM-PAC) (Haley et al. 2004) [22]. Computer Adaptive Testing uses a computer algorithm to pre-select the items that will be administered to a specific patient based on their responses to previous items. The AM-PAC measures functional outcome by using Item Response Theory (IRT). The AM-PAC Basic Mobility domain includes 101 items that address basic movement and physical functioning activities, such as bending, walking, carrying and climbing stairs. The AM-PAC Daily Activity domain includes 70 items that address basic self-care and instrumental activities of daily life.

Information about falls and hospital readmissions will be collected via interview at two-weeks and at three-months and confirmed via hospital records data.

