### Data collection

Balance and mobility will be assessed at baseline, two weeks and at three months after randomisation. Self reported physical functioning will be assessed at two weeks and at three months after randomisation. Information about falls and hospital readmissions will be collected at two weeks and at three months after randomisation. A proxy will be used for assessment of self reported physical functioning and fall/hospital readmission data if the assessor had significant concern over the reliability of information collected from the participant. Blinded assessors (experienced therapists) will conduct follow-up assessments.

Pre-morbid level of functioning (whether the participant could climb a flight of stairs and walk 800 m in the three months prior to hospital admission) and 12-month fall history will be collected during the baseline assessment. Medical records will be extracted to determine presenting diagnosis and demographic data.

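### Fall incidence is named as an outcome, but neither stated model estimates a rate, and the role of hospital records for falls after discharge is left open

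*Protocol article*

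**What the plan says.** Under Secondary outcomes the protocol article states: "Secondary outcomes will include mobility, self reported physical functioning, fall incidence and hospital readmissions". It does not say whether falls and readmissions are counts, rates or yes/no variables. Elsewhere its language is that of rates: the Background reports an earlier inpatient trial in terms of the incidence rate of falls, and the Discussion hopes for lower fall rates.

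The Statistical analysis section names two models. For the primary outcome and the secondary measures, between-group differences at the two "follow-ups will be analysed using ANCOVA models where baseline values are entered as covariates". In addition, "Dichotomous outcomes will be analysed via logistic regression models". No count model, person-time offset or time-to-event method appears.

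On ascertainment, Secondary outcomes says: "Information about falls and hospital readmissions will be collected via interview at two-weeks and at three-months and confirmed via hospital records data". Data collection allows for unreliable reports: "A proxy will be used for assessment of self reported physical functioning and fall/hospital readmission data" when the assessor doubts the participant's account. It also records that "12-month fall history will be collected during the baseline assessment", without making that history a covariate. The Intervention section shows that follow-up extends beyond the hospital stay: "Participants in both groups will receive usual multidisciplinary team care (e.g. outpatient therapy) after discharge".

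**The concern.** Two things do not fit together.

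First, the named outcome and the named models do not match. An incidence rate is events divided by time observed. ANCOVA compares means of an outcome adjusted for its baseline value. Readmissions have no baseline value, and falls have only a 12-month history that is not assigned to the model. Logistic regression can compare the proportion who fall at least once, but it treats one fall and five falls alike. Neither model uses the time a person was observed, and the Sample size calculation section expects 15% to drop out.

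Second, one sentence applies confirmation from hospital records to inpatient falls, falls after discharge and readmissions together. For readmissions and inpatient falls this is natural. A fall at home without hospital contact leaves no hospital record, and no rule says what happens to a reported fall that the records do not show.

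At stake are the information in the falls comparison, an effect measure that answers the question as worded, and a stable definition of a fall.

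**Working it through.** **No plan figure to reproduce.** The protocol gives no expected fall rate, dispersion or power for falls. Its sample size concerns balance only. The size of the problem can therefore only be illustrated under assumed values.

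**Inputs from the protocol.** 162 participants, so 162 / 2 = 81 per arm if allocation is 1:1 (the ratio is not stated); 15% dropout; a three-month window.

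**Assumed inputs.** Control mean μ of 0.4 or 0.8 falls per person in three months; dispersion k of 1 or 2, where variance = μ + kμ²; true rate ratio 0.6; early leavers go at a random point between 5% and 100% of the window, unrelated to their fall risk; two-sided test at 0.05; 1,000 simulated trials per scenario; no covariates.

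**How much a yes/no outcome ignores.** With full follow-up, P(any fall) = 1 − (1 + kμ)^(−1/k), and the share of falls that are repeat falls is 1 − P/μ.
- μ = 0.4, k = 1: P = 1 − 1/1.4 = 0.286; repeat share 1 − 0.286/0.4 = 29%.
- μ = 0.4, k = 2: P = 1 − 1.8^(−0.5) = 0.255; repeat share 36%.
- μ = 0.8, k = 1: P = 1 − 1/1.8 = 0.444; repeat share 44%.
- μ = 0.8, k = 2: P = 1 − 2.6^(−0.5) = 0.380; repeat share 53%.

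**Power at rate ratio 0.6 (%).** The linear column is a t-test on counts, standing in for ANCOVA without a true baseline.

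| μ | k | Linear | Logistic, any fall | Negative binomial, time offset | Negative binomial minus logistic |
|---|---|---|---|---|---|
| 0.4 | 1 | 30.3 | 24.8 | 30.2 | 5.4 |
| 0.4 | 2 | 24.4 | 20.1 | 26.0 | 5.9 |
| 0.8 | 1 | 47.3 | 32.2 | 50.4 | 18.2 |
| 0.8 | 2 | 34.9 | 23.2 | 39.0 | 15.8 |

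The loss from logistic regression is 5 to 18 points. The linear model loses at most 39.0 − 34.9 = 4.1 points; its weakness is that it yields no rate ratio and lacks the baseline it calls for. The simulation error of a single estimate is at most √(0.5 × 0.5 / 1000) = 1.6 points.

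**Type I error, 15% dropout in both arms.** Linear 3.7–4.7%, logistic 2.8–5.7%, negative binomial 4.6–5.0%. Poisson regression with an offset but no overdispersion term gave 8.9–20.3%, so it is not a substitute.

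**Unequal dropout, 5% versus 25% (μ = 0.8, k = 1, no true effect).** An early leaver is observed on average for (0.05 + 1)/2 = 0.525 of the window, so loses 0.475. Mean observed time is 1 − 0.05 × 0.475 = 0.976 in one arm and 1 − 0.25 × 0.475 = 0.881 in the other. The ratio is 0.881 / 0.976 = 0.90, so raw counts differ by about 10% with no effect of treatment. Type I error was 7.5% linear, 6.4% logistic and 5.4% negative binomial: a mild inflation under a deliberately wide imbalance.

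**Hospital records.** No arithmetic applies. Interviews cover falls up to three months, and part of that time is spent out of hospital. Confirmation from hospital records is stated for the whole period, with no rule for a mismatch.

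**The case against.** The best defence is that falls and readmissions are meant as yes/no outcomes. Balance, mobility and self-reported function are all scores, so falls and readmissions are the only listed outcomes that the logistic sentence can plausibly serve. Fall incidence would then be an incidence proportion and logistic regression a valid analysis. This stands as far as it goes: nothing in the document rules it out. But the document never defines the outcome that way, its own language elsewhere is of rates, and the ANCOVA sentence literally takes in the secondary measures.

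It can also be said that the assessment times are fixed and unequal time at risk is nowhere stated. That is right. Unequal observation is an inference from the expected dropout.

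A reader might go further in four ways that the document does not support:
- That the stated models give invalid tests. With equal dropout they do not in these simulations.
- That unconfirmed falls will be discarded. The text does not say so; interview or proxy is the first source.
- That most falls after discharge never reach a hospital. The document gives no figure for this.
- That readmission risk should be counted from discharge because an inpatient cannot be readmitted. Discharge follows randomisation and its timing may depend on treatment, so a clock starting there would weaken the intention-to-treat comparison. The window from randomisation should stay.

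Finally, falls were not a powered outcome. Even the better model reaches only 26% to 50% power in the scenarios tried.

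**Conclusion.** The concern holds in a limited form. If fall incidence means a rate, as the document's wording suggests, neither named model estimates it or uses observation time. If it means any fall, logistic regression is admissible but sets repeat falls aside, at a cost of roughly 5 to 18 points of power for a rate ratio of 0.6. That range rests entirely on assumed values: 0.4 to 0.8 falls per person, dispersion 1 to 2, and dropout unrelated to fall risk. It would change with the real fall rate.

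The role of hospital records for falls after discharge is ambiguous; whether any falls would be lost depends on whether confirmation is used as a filter. Both matters concern secondary outcomes, and the conclusion on balance is unaffected. The change is worth making because it is cheap.

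**What to change.** - Define the main falls outcome as the number of falls from randomisation to three months. Analyse it by negative binomial regression with a log(days observed) offset, adjusted for the 12-month fall history already collected, and report an incidence rate ratio with its confidence interval.
- Keep logistic regression for the proportion with any fall and the proportion with any readmission, both counted from randomisation.
- State that, for falls after discharge, hospital records are an additional source and not a condition for counting a fall reported by the participant or proxy.

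The cost is a few sentences of analysis wording and a last-contact date for each participant. The downside is that some unverified self-reported falls will be counted.
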